## Abstract

**Introduction:**

Metabolic dysfunction-associated steatotic liver disease (MASLD) is a progressive condition that may lead to liver cirrhosis and hepatocellular carcinoma. It is strongly associated with cardiometabolic diseases such as type 2 diabetes (T2D) and obesity. Weight loss is a key therapeutic strategy to treat MASLD. In recent years, there has been increasing attention to weight-reducing medication, but promising dietary interventions—such as early time restricted eating (eTRE)—have also been developed. Whether these dietary interventions are a good alternative to weight-reducing medication remains unclear, as direct comparative studies are still lacking. Therefore, this study will compare the effects of an early time restricted eating Mediterranean diet (eTRE-MD) intervention with naltrexone/bupropion (N/B) treatment on liver fibrosis, measured as liver stiffness (LSM) by transient elastography, in individuals with cardiometabolic risk factors.

**Methods and analysis:**

We will conduct a randomised controlled trial with a planned sample size of 70 overweight (Body mass index, BMI >27 kg/m2) adults aged 18–75 years with T2D, hypertension, dyslipidaemia or obesity and moderate to severe liver fibrosis, measured as LSM (>7.0 kPa and <13.6 kPa). The diet group will receive eTRE-MD, with a 10-hour eating time restriction (8AM–6PM). The medication group will receive 32 mg/360 mg of N/B (after a dose increase period following Summary of Product Characteristics). The main study endpoint is the between-group difference in liver fibrosis (kPa) from baseline to 6 months. Secondary endpoints are liver steatosis, weight, body composition, cardiovascular risk factors, quality of life, patient satisfaction and compliance. General linear models for repeated measurements will be applied for statistical analysis of the data.

**Ethics and dissemination:**

Ethical approval from the Medical Research Ethics Committees United (MEC-U) has been obtained. The results of the study will be submitted for publication in a peer-reviewed journal.

**Trial registration number:**

NCT06845345.

Strengths and limitations of this studyThis study uses a randomised controlled design to compare two active interventions.The planned sample size provides adequate statistical power to detect between-group differences.Blinding is not feasible because the interventions differ substantially, but the primary outcome is an objective clinical measure with low risk of bias.Liver steatosis and fibrosis are assessed using transient elastography rather than liver biopsy, which is the diagnostic gold standard.

## Introduction

 Metabolic dysfunction-associated steatotic liver disease (MASLD) is a progressive disease ranging from liver steatosis to more severe metabolic dysfunction-associated steatohepatitis (MASH). This involves damage to hepatocytes, resulting in a healing process in which scar tissue (fibrosis) is formed. In severe cases, fibrosis can lead to cirrhosis, hepatic failure or even hepatocellular carcinoma. Recent data suggest that MASLD may be present in approximately 30% of the adult world population.^1 2^ However, the prevalence of MASLD in high-risk patients such as individuals with type 2 diabetes (T2D) or dyslipidaemia can be as high as 50%.^3 4^ Besides the risks of serious liver disease, people with MASLD have a higher cardiovascular risk.^5 6^

Lifestyle modification–including weight loss, dietary changes, physical exercise and discouraging alcohol consumption–is currently the primary recommended treatment for MASLD according to the latest guidelines from the European Association for the Study of the Liver (EASL).^7^ Most guidelines highlight the Mediterranean diet as an effective dietary intervention for MASLD. A recent meta-analysis supports this recommendation, showing that the diet significantly reduces liver fat and insulin resistance in individuals with MASLD, independent of weight loss or amount of visceral fat.^8^ Furthermore, long-term adherence to the Mediterranean diet combined with carbohydrate restriction appears more effective in reducing liver fat than a fat restricted diet alone.^9^ In addition to the Mediterranean diet, other nutritional strategies have shown promise. Caloric restriction through intermittent fasting may benefit individuals with MASLD.^10^ Observational studies suggest that shifting food intake to earlier in the day is associated with a lower risk of fatty liver disease, and that intermittent fasting improves hepatic outcomes in people with T2D.^10 11^ Intermittent fasting is an umbrella term that encompasses a range of dietary interventions aimed at extending the fasting period. Among these interventions, eTRE—which limits the daily eating window to less than 10 hours, ending in the late afternoon—seems to be the most promising strategy. In a 2-week proof-of-principle controlled eating study, eTRE led to significant improvements in metabolic health, including glycaemic markers, among overweight prediabetic men, independent of changes in body weight.^12^ Additional evidence suggests that eTRE enhances insulin sensitivity and glycaemic control in individuals with T2D and promotes weight reduction in people with obesity.^13^,^16^ Given that weight loss remains a cornerstone in the management of MASLD, these findings are clinically relevant. Histological data indicate that a 3%–5% reduction in body weight can improve liver steatosis, while losses exceeding 10% may lead to regression of steatohepatitis and fibrosis.^17^ Despite these promising outcomes, only a limited number of randomised controlled trials have evaluated the effects of eTRE in individuals with MASLD. Current evidence supports its efficacy in reducing intrahepatic fat; however, its impact on liver fibrosis has not yet been clarified.^18 19^ A recent 12-week intervention combining eTRE with a hypocaloric Mediterranean diet demonstrated a significant reduction in liver fibrosis, though the short duration limits conclusions regarding long-term effects.^20^ Therefore, further long-term research is needed, combining eTRE with a Mediterranean diet to investigate the most potential dietary strategy for people with MASLD.

Besides dietary strategies, pharmaceutical interventions are increasingly being explored as effective options for the treatment of MASLD. Recently, resmetirom was approved by both the US Food and Drug Administration (FDA) and the European Medicines Agency (EMA) as the first pharmacological agent specifically indicated for the treatment of liver fibrosis in people with MASH.^21 22^ Other promising agents include glucagon-like peptide 1 (GLP-1) receptor agonists such as semaglutide, originally developed for obesity and cardiovascular risk reduction, which has now also been approved for the treatment of MASH in adults with moderate to advanced liver fibrosis.^23^ In parallel, several pharmacological treatments are already available to support weight loss, which remains a cornerstone in MASLD management. Currently approved medications for obesity in adults include orlistat, liraglutide, semaglutide and naltrexone/bupropion (N/B).^24^ Although all four have demonstrated efficacy in reducing body weight, N/B may be considered favourable due to its oral administration and relatively lower cost. N/B reduces hunger and enhances satiety, ultimately promoting weight loss. A long-term study showed that patients treated with N/B lost significantly more weight compared with placebo, and those achieving ≥5% wt loss after 16 weeks were more likely to maintain this reduction after 1 year.^25^ Despite these benefits, side effects such as nausea, constipation, vomiting, diarrhoea and dry mouth may occur. Importantly, agents such as semaglutide and resmetirom have direct cardiometabolic and liver-specific effects beyond weight reduction, making it difficult to attribute changes in liver fibrosis to weight loss alone. In contrast, N/B induces weight loss without known hepatic benefits, making it an appropriate comparator for evaluating weight-loss driven effects on MASLD, which is the aim of the current study.

To the best of our knowledge, the effectiveness of dietary intervention compared with weight loss medication has not been evaluated in people with MASLD, as pointed out in the most recent EASL guideline for MASLD.^7^ Because both lifestyle modification and pharmacological therapy are considered primary treatment strategies—and individual patients may respond differently to each—direct comparison of these approaches may help clarify their relative effectiveness and inform clinical decision-making. This study aims to compare the pharmacological treatment with N/B with a dietary intervention combining eTRE with a Mediterranean diet (eTRE-MD). We hypothesise that the eTRE-MD intervention will be more effective than N/B in reducing liver fibrosis in individuals with MASLD.

### Objectives

The primary objective of this study is to determine the difference in effectiveness of an eTRE-MD compared with naltrexone/bupropion (N/B) during 6 months on liver fibrosis, measured as liver stiffness (LSM) by transient elastography, in individuals with one or more cardiometabolic risk factors and overweight. Given that liver fibrosis is the strongest prognostic marker for adverse outcomes in MASLD, LSM is the primary objective. This study intentionally targets a more advanced MASLD population, as there is limited evidence on the effects of dietary interventions in individuals with established fibrosis. Steatosis will also be analysed to enable comprehensive phenotyping and to examine its relationship with changes in LSM and metabolic outcomes.

The secondary objectives of this study are:

To compare the effect of eTRE-MD vs N/B on liver steatosis during 6 months in individuals with one or more cardiometabolic risk factors and overweight.To determine the difference in weight loss and body composition between eTRE-MD and N/B during 6 months.To determine the difference in cardiovascular risk factors and biomarkers associated with MASLD between eTRE-MD and N/B during 6 months.To determine the difference in lifestyle factors between eTRE-MD and N/B during 6 months.To evaluate the difference in quality of life, treatment satisfaction, compliance and adherence between eTRE-MD and N/B during 6 months.

## Methods and analysis

### Patient and public involvement

Patient organisations were involved in the development of this study. The current research proposal has been submitted to the Dutch Diabetes Association (DVN), the Dutch Liver Patients’ Association (NLV) and the European Liver Patients’ Association (ELPA) for comment and support. They have provided feedback on the proposal, taking the patients’ interests into account.

### Trial design

This study is a randomised controlled trial with a duration of 6 months. After signing informed consent, eligible participants will be randomised to eTRE-MD or N/B. Details of the informed consent form are presented in online supplemental file 1. Outcome parameters will be measured at baseline, 3 months and 6 months. Figure 1 shows the flowchart of this study.

**Figure 1 F1:**
[figure not shown]
Flowchart of the trial. eTRE, early time restricted eating; LSM, liver stiffness measurement.

### Trial setting

People with obesity or overweight and T2D, hypertension or dyslipidaemia, and moderate to severe liver fibrosis will be recruited from the outpatient clinic of the Franciscus hospital in Rotterdam and general practitioners in Rotterdam, The Netherlands. The study started in April 2025 and is expected to be completed in July 2027.

### Eligibility criteria

Inclusion criteria are:

Body mass index (BMI) >30 kg/m2 or BMI >27 kg/m2 and at least one cardiometabolic risk factor (T2D, hypertension, dyslipidaemia).Moderate to severe liver fibrosis, measured as LSM by transient elastography (>7.0 kPa and <13.6 kPa).Aged 18–75 years.Written informed consent,

Exclusion criteria are:

An insufficient comprehension of the Dutch language (spoken and written).Pregnancy, breast-feeding or intention to become pregnant.Participants with an established diagnosis of liver pathology like, but not limited to:Hepatitis B.Hepatitis C.Autoimmune hepatitis.Wilson’s disease.Haemochromatosis.Primary biliary cholangitis.Primary sclerosing cholangitis.Alcoholic liver disease.History of liver transplant, or current placement on a liver transplant list.History of cirrhosis and/or hepatic decompensation, including ascites, hepatic encephalopathy or variceal bleeding.Participants with active HIV infection and/or treatment.Participants with diagnosed malignancies with or without active treatment.Participants with history or pre-existing renal disease (estimated Glomerular Filtration Rate (eGFR) <30 mL/min/1.73 m^2^).Participants with corticosteroid induced diabetes (while still using corticosteroids).Participants using GLP-1 agonists for less than 3 months or not yet on a stable dose.Participants using Monoamine Oxidase inhibitors, opioids and/or methadone (due to contraindication).Known or suspected excessive alcohol consumption (>30 grams/day for males or >20 grams/day for females. One drink is equivalent to 10 grams of alcohol).Previous or planned (during the trial period) obesity treatment with bariatric surgery. However, previous interventions that have resulted in stable weight for at least the past 3 months are allowed.Participants with a history or evidence of any other clinically significant condition or planned or expected procedure that in the opinion of the investigator, may compromise the patient’s safety or ability to complete the study.

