#### Medication group

The medication used in the study is N/B to ensure that the comparator reflects weight loss alone, without any additional metabolic or liver-specific pharmacological effects. Participants in the medication group will take N/B (Mysimba) two times per day at a total dose of 32 mg/360 mg N/B per day for a duration of 6 months. The dosage will be built up in the first month following the stepped care approach used in the Summary of Product Characteristics (SmPC), up to maximally tolerated doses. Compliance with N/B intake is monitored by pill counting at the 3-month and 6-month visits. Participants are asked to bring all medicine packaging to each visit, and the number of remaining tablets is recorded by the researcher. Adherence is defined a priori as taking at least two tablets per day, with dose adjustments permitted based on individual tolerance. They receive usual care, including the advice of 60 min of exercise per day and standard dietary recommendations according to the guidelines for the Dutch population.^28^ During the visits at baseline, 3 months and 6 months, medication use and usual care will be evaluated by a physician in the hospital. Participants will wear the Activ8 Activity Tracker GEN2 at baseline and at the end of the study.

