### Outcomes

The main study parameter is the between-group difference in absolute change in liver fibrosis during 6 months. Liver fibrosis will be measured as LSM (kPa) by transient elastography (FibroScan).

Secondary study parameters are as follows:

Absolute change in liver steatosis (Controlled Attenuation Parameter score, FibroScan).Nutritional assessment: body weight (kg, Seca 888 compact digital flat scale), height (cm), waist circumference (cm), fat mass and lean body mass measured with bioelectrical impedance analysis (kg, Bodystat 500), grip strength (kg, Jamar).Cardiovascular risk factors: total cholesterol, low-density lipoprotein cholesterol, high-density lipoprotein cholesterol, triglycerides, apolipoprotein B (ApoB), apolipoprotein AI (ApoAI), lipoprotein (a), Hemoglobin A1c, fasting blood glucose, fasting insulin and blood pressure, measured with routine lab procedures.Other laboratory measurements, measured with routine lab procedures. Among others, the following routine measurements will be done: creatinine, eGFR, alanine aminotransferase (ALAT), aspartate aminotransferase (ASAT), thrombocytes, haemoglobin (Hb), leucocytes, transferrin, ferritin, total iron binding capacity, apolipoprotein B48 (ApoB48), fibroblast growth factor 19 (FGF19) and 21 (FGF21), C-reactive protein (CRP), fibrosis-4 index score (Fib-4), thyroid-stimulating hormone (TSH), free thyroxine 4.Physical activity (Activ8 Activity Tracker GEN2).Quality of life (36-Item Short Form Health Survey Questionnaire).^29^Patient satisfaction in case of T2D (Diabetes Treatment Satisfaction Questionnaire).^30^Food intake and adherence to the dietary intervention (3-day food diary).Demographic variables, drug use, smoking and drinking habits, medication use and compliance to the time restriction (self-developed questionnaire).

Other study parameters are as follows:

Shift in liver fibrosis severity (categorised in fibrosis score F0-F3).Side effects (self-reported).Number of participants that drop-out (categorised by reason for drop-out).

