### Statistical methods

All analyses will be conducted according to the intention-to-treat and per protocol principle. To be included in the per protocol analysis, a participant is required to have at least data available for two time points (baseline and T1 or T2) and to achieve 80% or higher adherence. Participants of the eTRE-MD group are considered adherent to the dietary protocol if they restrict their daily food intake to a window of less than 10 hours—specifically between 7:30 AM and 6:30 PM—on at least 5 days per week. Additionally, they must maintain a daily caloric intake that is at least 400 calories below their estimated energy requirement. Participants of the N/B group are considered adherent to the medication protocol if they consistently take a minimum of two tablets per day, with the exact dosage adjusted according to individual tolerance levels. These adherence data will be used to classify participants for the per protocol analysis and to explore the impact of medication compliance on treatment outcomes. All other non-compliant participants will be excluded from the per protocol analysis. Normality of the data and homogeneity of variances will be tested using Shapiro-Wilks test and Levene’s test. For numerical data, we will use the mean (in case of normal distribution) and median values (in case of non-normal distribution), with respectively the SD and IQR as measures of dispersion.

The primary outcome will be defined as the absolute change in liver fibrosis during 6 months. The difference in liver fibrosis change between the eTRE-MD group and N/B group will be analysed with a linear mixed model adjusted for baseline, with independent variables treatment arm, time point (T1 and T2), and the interaction between treatment arm and time point. The estimated difference between treatment arms in the liver fibrosis change at T2 (6 months) will be calculated using the estimated marginal means. Mixed modelling can efficiently handle data with missing and unbalanced time-points. It corrects for bias when absence of data is dependent on characteristics that are present in the models (missing at random, MAR). The secondary outcomes will be analysed with a linear mixed model adjusted for baseline, with independent variables treatment arm, time point (T1 and T2), and the interaction between treatment arm and time point. The estimated difference between treatment arms will be calculated using the estimated marginal means.

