To account for heterogeneity in metabolic profiles, cardiometabolic condition (type 2 diabetes, hypertension, dyslipidaemia or obesity) will be included as a covariate in all primary and secondary outcome analyses. Outcomes will be analysed using linear mixed models with treatment arm, time point (T1 and T2), and their interaction as fixed effects, adjusted for baseline values. An interaction term between treatment arm and cardiometabolic condition will be explored to assess potential differential treatment effects across subgroups. Given the limited sample size, stratified analyses will not be performed unless sufficient power is available. Participants with multiple conditions will be included in the overall model and appropriately coded for subgroup membership. Sensitivity analyses may be conducted to evaluate the robustness of findings in overlapping vs non-overlapping subgroups.

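### Stable GLP-1 agonist users may enter either arm, but the stated primary model has no term for their use, which costs precision and leaves chance imbalance uncorrected

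*Protocol article*

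**What the plan says.** Under Eligibility criteria, the exclusion covers "Participants using GLP-1 agonists for less than 3 months or not yet on a stable dose". Anyone on a stable dose for 3 months or longer can therefore be randomised to diet or to naltrexone/bupropion (N/B).

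The Introduction refers to "glucagon-like peptide 1 (GLP-1) receptor agonists such as semaglutide" and states that "agents such as semaglutide and resmetirom have direct cardiometabolic and liver-specific effects beyond weight reduction". It gives this as the reason for not using such an agent as comparator. The Medication group section repeats the reasoning: N/B was chosen "to ensure that the comparator reflects weight loss alone, without any additional metabolic or liver-specific pharmacological effects".

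Statistical methods specifies a "linear mixed model adjusted for baseline, with independent variables treatment arm, time point (T1 and T2" and the interaction of arm and time. It adds that "cardiometabolic condition (type 2 diabetes, hypertension, dyslipidaemia or obesity) will be included as a covariate" in all primary and secondary analyses. No term for GLP-1 agonist use is named. The only sensitivity analyses mentioned concern participants who fall into one or several cardiometabolic subgroups.

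Randomisation is 1:1 in blocks of 2, 4 and 6, with no stratification factor stated. The Outcomes section lists "medication use and compliance to the time restriction (self-developed questionnaire", and Table 1 schedules the questionnaire that covers medication at baseline, 3 months and 6 months.

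**The concern.** By the protocol's own account, at least one GLP-1 agonist acts directly on the organ in which the primary outcome is measured. If stable users continue to change differently from non-users over the 6 months, GLP-1 use is a prognostic factor for LSM change. The trial randomises 70 people, so the share of users can differ between arms by chance, and the stated model would not correct the estimate for it. The same factor also leaves variance unexplained that one covariate could remove.

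The cardiometabolic covariate covers this only in part. Type 2 diabetes is an imperfect proxy for GLP-1 use: not every participant with diabetes need be a user, and the Introduction notes that semaglutide is also used for obesity and for steatohepatitis.

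There is also a mismatch of reasoning. The comparator was chosen to work through weight loss only, yet the eligibility text allows background use of a drug class to which the Introduction attributes further liver effects.

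**Working it through.** **Inputs from the protocol (Sample size and recruitment).** Target difference 0.8 kPa; SD 1.0 kPa; two-sided alpha 0.05; power 0.80; 29 per group needed; 35 per group randomised.

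**Assumptions, not in the document.** Share of stable GLP-1 users, p: 10%, 20% or 30%. Difference between users and non-users in 6-month LSM change, g: 0.5 to 1.0 kPa.

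**Step 1: the plan's own figure.** The normal approximation gives 2 × (1.96 + 0.84)² × 1.0² / 0.8² = 24.5, so 25 per group. The exact t-test gives 25.5, so 26. The stated 29 is not reproduced, but it errs on the safe side: 29 per group gives 85% power. This is a separate matter and does not affect what follows.

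**Step 2: chance imbalance.** Randomising 70 people into two arms of 35, the difference in share of users has SD = √(4p(1−p)/69) (hypergeometric). The shift in the unadjusted estimate is that difference times g.

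| Users | SD of imbalance | 95% range | Shift, g = 0.5 | Shift, g = 1.0 |
|---|---|---|---|---|
| 10% (7 of 70) | 7.2 points | ±14 points | ±0.07 kPa | ±0.14 kPa |
| 20% (14 of 70) | 9.6 points | ±19 points | ±0.09 kPa | ±0.19 kPa |
| 30% (21 of 70) | 11.0 points | ±22 points | ±0.11 kPa | ±0.22 kPa |

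With 58 analysed instead of 70, the extremes are ±0.08 and ±0.24 kPa.

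The chance of an imbalance of 10 points or more among 70 is 11%, 37% and 30% for 10%, 20% and 30% users. The figures are not monotone because counts are whole numbers. For 20 points or more it is 1%, 3% and 12%.

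**Step 3: comparison.** The standard error with 29 per group is √(2/29) × 1.0 = 0.26 kPa. The 95% limits of the shift are therefore 0.07/0.26 = 0.3 to 0.22/0.26 = 0.8 of a standard error, or 9% to 27% of the 0.8 kPa target.

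**Step 4: type I error.** A simulation with 29 per arm, g = 1.0 and no treatment effect gave 0.050 (20% users) and 0.052 (30% users) over all randomisations. In the randomisations with an imbalance of 20 points or more, the rejection rate was 11% and 12%.

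**Step 5: precision.** GLP-1 use contributes variance p(1−p)g², from 0.1 × 0.9 × 0.5² = 0.02 to 0.3 × 0.7 × 1.0² = 0.21.
- If the SD of 1.0 is the total SD, adjustment lowers the residual SD to √(1 − 0.02) = 0.99 down to √(1 − 0.21) = 0.89. Power with 29 per group rises from 85% to 86-92%.
- If 1.0 is the SD within users and within non-users, the total SD is 1.01 to 1.10. Power without adjustment is 78-84% instead of 85%.

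None of these figures credits the existing baseline and cardiometabolic covariates, so they are upper values for the assumed inputs.

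**The case against.** The strongest reply is that randomisation already deals with this. GLP-1 use is balanced in expectation, and the standard error covers chance imbalance in any unadjusted factor. That stands: Step 4 shows a valid test overall, and the 11-12% applies only to an uncommon subset of randomisations. A reader might infer that the result would be biased or the test invalid; the document does not support that.

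Second, part of the effect is already absorbed. The exclusion removes recent and unstable users, any effect reached before enrolment sits in the baseline LSM, and diabetes is in the model. This also stands. It shrinks the problem but does not remove a drug effect that continues during follow-up.

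Third, a reader might put the shift as high as 40% of the target. That needs 30% users, the edge of the 95% imbalance range and a 1.5 kPa differential together (0.21 × 1.5 = 0.32 kPa; 0.32/0.8 = 40%). A differential of 1.5 kPa exceeds the 1.3 kPa change assumed for the whole diet arm, yet would be assigned to people already stable on treatment. It is not a fair planning value.

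Fourth, a reader might conclude that background GLP-1 use invalidates the comparison with N/B. It does not. Use is permitted equally in both arms and the endpoint is a between-arm difference. What suffers is the reading of change within an arm as driven by weight loss only.

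Finally, this is a condensed article and a statistical analysis plan may say more. Its silence on stratification does not prove that there is none. The covariate set, however, is stated for all primary and secondary analyses, and it leaves out a factor that the Introduction itself singles out.

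**Conclusion.** The point holds as a modest one about precision and chance imbalance. The eligibility text admits stable users, the Introduction attributes direct liver effects to semaglutide, and the stated model has no term for GLP-1 use. The consequence is not systematic bias, and overall type I error remains at about 5%.

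Under the assumed 10-30% users and 0.5-1.0 kPa differential, the 95% limits of the shift run from about ±0.07 to ±0.22 kPa, always below the standard error of about 0.26 kPa. Both assumptions come from outside the document. The differential is the weaker of the two: the protocol's statement names semaglutide, not every GLP-1 agonist, and gives no size for any further change in stable users. If the differential is near zero, so is the problem.

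The adjustment is still worth making because it is almost free and has to be fixed before the data are seen. Added after an imbalance is found, it would be post hoc.

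**What to change.** Pre-specify baseline GLP-1 agonist use (yes/no), taken from the baseline medication questionnaire, as a fixed covariate in the primary model beside baseline LSM and cardiometabolic condition. Add one supportive sensitivity analysis that leaves out participants who were users at baseline. Do not exclude participants for starting or changing such a drug after randomisation: response to the allocated treatment may influence those events, so excluding on them could create the imbalance that the analysis is meant to guard against.

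Reconcile the stated reason for choosing N/B (Introduction and Medication group) with the exclusion criterion, for example by saying that the reason concerns the randomised comparator and how background GLP-1 use is to be read. Whether stable users should be eligible is a clinical question that this review does not address.

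The cost is 1 degree of freedom, one extra analysis and a few lines of text, with no new data collection.
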